**Fig. 1 Fig1:**
[figure not shown]
MEFAP Project Design**.** MEFAP: Multicomponent physical activity program (for its acronym in Spanish)

**Table 1 Tab1:** Schedule of enrollment, interventions, and assessments in MEFAP Project

TIMEPOINT	Enrolment	Allocation				End of Study
	*-t* _*1*_	0	*t* _*1 baseline*_	*Intervention*	*t* _*2*_ *6 –months post-intervention*	*t* _*3*_ *12–months post-intervention*
ENROLMENT						
Eligibility screen	X					
Informed consent	X					
Randomized Allocation		X				
INTERVENTION						
INTERVENTION GROUP: *Multicomponent Exercise Program (MEFAP)*				X		
*CONTROL GROUP: Regular Clinical Practice*				X		
ASSESSMENTS						
***Main outcome variables:***						
*● Frailty level (Fried Criteria)*	X		X		X	X
*Secondary outcome variables*						
*● Function-related variables: SPPB, risk of falls*			X		X	X
*● Quality of life*			X			X
*● Clinical Parameters:*						
✓ Blood pressure			X		X	X
✓ BMI			X		X	X
✓ Cognitive state (MEC30 Lobo)			X		X	X
✓ Mood (Yesavage test)			X		X	X
✓ Chronic-use drugs (last 2 weeks).			X		X	X
✓ Chronic pain						
*● Analytical Parameters (metabolic and inflammation).*					X	X
*● Program adherence and satisfaction level*			X			X
*Independent Variables*						
*● Sociodemographic*			X			
*● Comorbidity o diagnosis of ≥ 2 chronic disease*			X			
*● Fracture in previous 5 years*			X			

*MEFAP:* Multicomponent physical activity program (for its acronym in Spanish), *SPPB* short physical performance battery, *BMI* Body Mass Index, *MEC30 Lobo* Mini-mental Exam Cognitive (Translated and adapted to Spanish by Lobo et al. 2002 [33])

### Study participants

The study population is composed of non-dependent, pre-frail elderly patients over the age of 70 and attending the participating health centers.

### Inclusion criteria

Following the 2014 Consensus Document on the prevention of frailty and falls in the elderly patient [29] we will recruit individuals > 70 years of age, with a Barthel test score ≥ 90 and meeting at least one of the following two criteria: a score between 9 and 11 in the short physical performance battery (SPPB) [30] or FRAIL questionnaire with values 1 or 2 [31, 32]. At baseline (t1), pre-frail patients will be included (1 or 2 frailty criteria according to Fried: unintentional weight loss, exhaustion, weakness, slowness, and low physical activity) [4].

### Exclusion criteria

Inability to go to the Primary Care Health Center for any reason.Moderate to severe cognitive impairment (MEC 30 Lobo ≤21) [33].Severe pathology for which physical activity is contraindicated at the physician’s discretion including but not limited to: recent acute myocardial infarction (6 months), uncontrolled cardiac arrhythmia, severe cardiac valve disease, non-controlled hypertension (> 180/100), non-controlled/severe heart failure, severe respiratory insufficiency disease, and diabetes mellitus with acute decompensation/frequent hypoglycemia.

### Sample size

We calculated the sample size based on two data points: the published figure of 15% of pre-frail individuals that transition to robust status in the absence of an intervention [12] and our 35% estimated percentage of pre-frail elderly in the intervention group becoming robust again. Therefore, we expect a difference of 20% of favorable evolution (from pre-frail to robust) between both control and intervention groups. Considering a power of 80% and an alpha of 0.05, the sample size would be 146 patients (73 patients in the intervention group and 73 patients in the control group). Assuming an attrition of 30%, the final number needed to recruit is 190 patients (*n* = 95 in IG and *n* = 95 in CG).

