**Methods:**

Randomized parallel group multicenter clinical trial located in primary care setting, among non-dependent and pre-frail patients > 70 years old, including 190 patients (95 intervention, 95 control group). Intervention: Multicomponent physical activity program (MEFAP, for its acronym in Spanish) with twelve 1.5 h-weekly sessions comprised of: 1. Informative session; 2. Exercises for improving aerobic resistance, muscle strength, propioception-balance and flexibility; and 3. Handing out of at-home exercise chart (twice/week). Main variable: pre-frailty according to the Fried phenotype. Secondary variables: sociodemographic, clinical and functional variables; exercise program adherence, patient satisfaction with the program and quality of life. We will perform an intention-to-treat analysis by comparing the retrogression from pre-frailty (1 or 2 Fried criteria) to robust status (0 Fried criteria) by the end of the intervention, 6 months and 12 months post-intervention. The accumulated incidence in each group will be calculated, as well as the relative risk (RR) and the number needed to treat (NNT) with their corresponding 95% confidence intervals. Protocol was approved by the Ethics Committee Hospital la Paz.

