### Main analysis of effectiveness

Data will be analyzed using intention-to-treat analyses.

A positive event for the main outcome variable, intervention effectiveness, will be defined as the transition from pre-frailty (1 or 2 Fried criteria) to robust status (zero Fried criteria) during the study period. The accumulated incidence in each group, the relative risk (RR), the number-needed-to-treat (NNT) will be calculated, with their corresponding 95% confidence intervals. We will perform the analysis with the statistical programs SPSS v.24.

Outcome evaluation (changes in frailty) and statistical analyses will be conducted by skilled study staff blind to treatment allocation.

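### 190 randomised patients do not leave the required 146 after 30% attrition; power is then about 76.5%, not 80%

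*Protocol article*

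**What the plan says.** All the figures are in the Sample size section of the protocol article.

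- Control rate: "the published figure of 15% of pre-frail individuals that transition to robust status in the absence of an intervention".
- Intervention rate: "our 35% estimated percentage of pre-frail elderly in the intervention group becoming robust again", a difference of 20 percentage points.
- Evaluable sample: "Considering a power of 80% and an alpha of 0.05, the sample size would be 146 patients", split equally as "73 patients in the intervention group and 73 patients in the control group".
- Recruitment total: "Assuming an attrition of 30%, the final number needed to recruit is 190 patients", that is 95 per arm.

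The Methods part of the Abstract repeats the total: "including 190 patients (95 intervention, 95 control group". The article prints no formula for the step from 146 to 190. Under Main analysis of effectiveness it specifies intention-to-treat and says nothing about patients whose outcome is missing.

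**The concern.** An attrition of 30% means that 70% of those recruited remain. A recruitment total that covers it must therefore leave at least 146 when multiplied by 0.70. The printed total looks instead like 146 with 30% of itself added on, which covers a smaller loss than the one assumed.

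If so, the trial would miss its power target under the sponsor's own planning assumption, even with recruitment complete and attrition exactly as foreseen. Readers, funders and the ethics committee would take 190 patients to secure 80% power at 30% attrition.

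**Working it through.** **Inputs** (all from the Sample size section): p₁ = 0.35, p₂ = 0.15, difference 0.20, alpha 0.05, power 0.80, equal arms, attrition 30%, total 190. The section does not say whether alpha is one- or two-sided; the first step shows that two-sided is what was used.

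**1. Reproduce the 146.** Two-sided comparison of two proportions, pooled variance under the null, mean rate 0.25:

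n per arm = [1.96 × √(2 × 0.25 × 0.75) + 0.8416 × √(0.15 × 0.85 + 0.35 × 0.65)]² / 0.20²

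= [1.96 × 0.6124 + 0.8416 × 0.5958]² / 0.04 = (1.2002 + 0.5014)² / 0.04 = 72.4, rounded up to 73.

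Two arms give 146, an exact match. Other common versions do not give 73 per arm:

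| Version | n per arm |
|---|---|
| Two-sided, pooled | 73 |
| Two-sided, unpooled | 70 |
| Two-sided, arcsine | 71 |
| Two-sided, continuity-corrected | 83 |
| One-sided, pooled | 57 |
| One-sided, continuity-corrected | 67 |

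**2. Check the attrition step.**

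- Added on: 146 × 1.3 = 189.8, rounded up to 190; per arm 73 × 1.3 = 94.9, rounded up to 95. Both match the article.
- Divided out: 146 / 0.70 = 208.6, rounded up to 209; per arm 73 / 0.70 = 104.3, rounded up to 105, so 210 with equal arms. Neither matches.
- Patients left from 190: 190 × 0.70 = 133, or 66.5 per arm. Shortfall: 146 − 133 = 13.
- Largest attrition at which 190 still leaves 146: 1 − 146/190 = 23.2%.

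**3. Power with what remains.** From the same pooled formula,

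power = Φ{[0.20 × √n − 1.96 × 0.6124] / 0.5958}

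- n = 73: (1.7088 − 1.2002) / 0.5958 = 0.854, power 80.3%.
- n = 66.5: (1.6310 − 1.2002) / 0.5958 = 0.723, power 76.5% (76.2% at 66 per arm, 76.8% at 67).
- Exact binomial enumeration of the uncorrected chi-square test: 76.8% at 66 per arm and 77.5% at 67, against 80.8% at 73.
- Unpooled formula at 66.5 per arm: 78.2%. That version is not the one behind the article's 73.

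**4. Does intention-to-treat change this?** Step 3 analyses only patients with an observed outcome. Suppose instead that all 190 are analysed and drop-outs are counted as not reverting, with 30% lost in each arm (an assumption; the article names no method). The rates become 0.35 × 0.70 = 24.5% and 0.15 × 0.70 = 10.5%, with 95 per arm. Power is then about 72%, lower still.

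**5. Check the alternative total.** 210 × 0.70 = 147, or 73.5 per arm, with power 80.6%.

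**The case against.** The strongest case on the other side accepts the arithmetic and disputes its importance.

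- *The gap is smaller than the uncertainty in the inputs.* With 133 patients, the pooled formula returns 80.0% power if the intervention rate is 36% rather than 35%, and 81.1% if the control rate is 14% rather than 15%. The 35% is the team's own estimate. This is true, and it limits how much weight the shortfall deserves. It does not make the printed figures agree with each other.
- *Attrition may stay below 30%.* The Intervention section plans a telephone call after one missed session, and the Discussion offers controls a later programme. At 23.2% or less, 190 is enough. But 30% is the allowance the sample size paragraph claims to cover.
- *No estimate is biased.* Also true: the relative risk, the number needed to treat and their intervals are unaffected apart from being less precise.
- *The multiplication by 1.3 is inferred.* Correct, since no formula is printed. The shortfall does not depend on the inference: 70% of 190 is 133 however 190 was reached.
- *The 80% is attached to 146 patients, where it is right.* Yes. What fails is the further claim that recruiting 190 preserves it at 30% attrition.
- *The power at 30% depends on how drop-outs are analysed.* This stands as a point of wording: any restated power should say that it refers to patients with an observed outcome.

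**Conclusion.** The concern holds. The base calculation of 73 per arm is correct; the attrition allowance is not. At the stated 30% attrition, 190 recruited leave 133 evaluable patients, and power is about 76.5% by normal approximation or about 77% by exact enumeration. The type II error therefore rises from 20% to about 23–24%.

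These power figures assume rates of 15% and 35%, a two-sided test at 0.05, attrition equal in the two arms and unrelated to outcome, and an analysis of patients with an observed outcome. The 13-patient shortfall needs none of these assumptions. The effect on the trial is modest, but a figure that justifies the recruitment target is wrong as written and simple to correct.

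**What to change.** Choose one of two corrections.

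1. **Keep 190 and restate the justification.** For example: *190 randomised patients (95 per arm) give 80% power if attrition is at most 23%; with 30% attrition, 133 patients have an observed outcome and power in those patients is about 76%.* This costs one sentence in the Sample size section and a slightly less favourable power figure. The Abstract can stay as it is.
2. **Keep 80% power at 30% attrition and raise the target to 210** (105 per arm; 209 if equal arms are not required). This means 20 more patients, and the Abstract and the Sample size section must change together.

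The Trial registration section dates the first enrolment to July 2018, so the first option is the one that is clearly cheap. If the analysis is to count drop-outs as not reverting, the restated power should be worked out on that basis (about 72% with 190, under the assumption of 30% loss in each arm).

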### Recruitment

#### Primary Care Health Centers

All 32 Primary Care Health Centers (HC) in the Northern Primary Care Health Directorate of the Community of Madrid referring patients to the 7 physiotherapy units available in this catchment area will be offered to participate in the study. The principal investigator will contact and recruit each center personally.

#### Patients

Participating HC’s doctors and nurses will recruit patients > 70 years of age consecutively until reaching their HC’s patient quota (10–15 patients). The preselection in clinical consultation will be performed with the Barthel test, the SPPB, and the Frail questionnaire as an approach to the Fried frailty criteria, following the recommendations of the Consensus on the prevention of frailty and falls in the elderly, published in 2014 by the Spanish Ministry of Health, Social Services and Equality [29]. Eligible participants will at this time sign an informed consent and make an appointment to fill out the baseline survey (t1).

#### Randomization

Patients will be randomized into IG or CG after completion of baseline data collection (t1) in an automated process included in the Electronic Data Collection Notebook (eDCN).

##### Outcome

ᅟ

### Study variables

a) Main Outcome: Change in patient’s frailty level from pre-frail to robust. Frailty status is based on Fried criteria [4]: low gait when walking 4 m, grip strength with the dominant hand measured with a dynamometer, unintentional weight loss > 5% of body weight in the past year, low energy (CES-D) [34], and low physical activity (Yale scale) [35]. Pre-frailty is defined as meeting 1 or 2 Fried criteria and robust status is defined as meeting none (0) of Fried criteria.

b) Secondary outcome variables: Variables related to physical functioning: short physical performance battery (SPPB) [30], risk of falls (measured according to consensus proposal on the prevention of frailty and falls [29]. Quality of life: Measure with the EuroQol questionnaire 5D-5 L [36]. Adherence to the program and degree of satisfaction: Patients will be considered to have a good MEFAP adherence when they have attended at least 75% of the sessions**.** With regard to satisfaction, the dimensions of communication, professional attitude, technical competence and accessibility will be evaluated based on a questionnaire created for this purpose and measured with a Likert scale.

Clinical parameters: blood pressure, BMI, Cognitive state (MEC30 Lobo) [33] mood (Yesavage test) [37], chronic pain, and any chronic drugs consumed in the last two weeks. Analytical parameters: blood count, glucose and glycated hemoglobin, lipid profile, iron metabolism (iron, ferritin, transferrin), vitamin D, vitamin B12, folic acid, total proteins, and albumin and inflammation markers (ESR, CRP and fibrinogen).

c) Independent variables. Sociodemographic**:** age, sex, educational level, economic level (monthly family income in euros), main professional occupation. Clinical: Fracture in the previous five years (specify if hip fracture), Comorbidity or diagnosis of at least 2 diseases from the following list: Heart disease (arrhythmia, heart failure or ischemic heart disease), cerebrovascular disease, diabetes mellitus, chronic lung disease (asthma, COPD or respiratory failure), chronic kidney disease, cancer, and osteoarthritis / limiting arthritis (i.e., affecting activities of daily living).

#### Intervention

Intervention Group (IG): The intervention, MEFAP, consists of a multicomponent physical activity program that includes 1) informative talk; 2) aerobic endurance exercises (walking), muscle strength, proprioception-balance and flexibility; and 3) flashcards with guidelines of home exercises for at least twice that week. This is a 12 session-intervention to take place on a weekly basis in the physical therapy units with each session lasting for an hour and a half. To reduce interprofessional variability in the intervention, the participating physiotherapists will be trained to standardized the delivery of the intervention. Control group (CG): Participants assigned to this group will receive the usual clinical practice.

All participants will receive a document with simple physical activity recommendations as well as their report with the results from all the clinical and analytical tests after the baseline interview. Attrition will be minimized by contacting participants by telephone after missing just one intervention session.

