Lowering frailty rates requires reducing inactivity, one of its main risk factors [10]. Both a 2012 and a 2014 meta-analysis studying fragile individuals showed that physical activity delays and even reverses frailty and disability [11, 12], improves cognitive status and promotes emotional well-being and socialization [13]. Specifically, multicomponent physical exercise programs comprised of muscle strength development, cardiovascular endurance, and joint mobility and balance, are the most effective interventions to delay disability and other adverse events as well as to maintain the highest degree of independence possible for each individual [14]. However, how different trials measure interventions varies which difficults results comparisons. Therefore, physical activity, insofar as it prevents and even reverses early stages of frailty, has the potential of averting falls, disability, and improving quality of life [15]. Not to be dismissed, mood enhancement and the socialization inherent to group exercise programs may also contribute to these benefits.

Furthermore, physical inactivity is also the primary cause of most chronic pathologies [16]. Therefore, it is of interest to analyze the evolution of the control parameters of these pathologies (especially those related to cardiovascular risk) usually monitored by primary care medical staff, from baseline through the follow-ups while performing physical exercise regularly for any substantial amount of time.

Other interventions such as increasing vitamin D levels, resolving an underlying anemia, or increasing protein intake have shown improvement in the elderly’s physical function, independently from regular exercise’s benefit, and should be implemented within the context of usual clinical practice [17].

In Spain, primary care, is not only the point of entry into the health system but it also provides accessibility to diverse strata of the population with low disease burden. Further, it offers continuity of care along with a comprehensive approach including disease prevention and health promotion [18]. Thus, primary care is ideally positioned to play a crucial role in this intervention program, through the maintenance and improvement of physical, cognitive, and social functioning among the elderly, as well as the promotion of individual self-care for as long as possible.

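### The sample size makes no allowance for clustering by unit or physiotherapist in the intervention arm, and no handling is described; if such clustering exists, simple RR and NNT intervals would be too narrow and power below 80%

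*Protocol article*

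**What the plan says.** Under Randomization, the individual patient is the unit allocated. Under Intervention, the active arm attends the programme in shared facilities: "This is a 12 session-intervention to take place on a weekly basis in the physical therapy units". The control arm receives usual practice. The recruitment text on Primary Care Health Centers gives the number of such facilities: health centres are "referring patients to the 7 physiotherapy units available in this catchment area". How many of the seven will run the programme, and how many patients will share a session, is not stated.

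The Intervention section recognises that delivery can differ between professionals and answers this with training. The Background says of such programmes in general that "mood enhancement and the socialization inherent to group exercise programs may also contribute to these benefits".

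The Sample size section starts from "the published figure of 15% of pre-frail individuals that transition to robust status in the absence of an intervention" and "our 35% estimated percentage of pre-frail elderly in the intervention group becoming robust again", and concludes: "Considering a power of 80% and an alpha of 0.05, the sample size would be 146 patients". That is 73 per arm, raised to 95 per arm for attrition. Main analysis of effectiveness then plans cumulative incidence by arm, and "the relative risk (RR), the number-needed-to-treat (NNT) will be calculated, with their corresponding 95% confidence intervals". It names no interval method and no term for unit, physiotherapist or group.

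**The concern.** This is a partially nested design: allocation is individual, but one arm is treated in clusters and the other is not. If some physiotherapists or groups get better results than others, patients who share them have correlated outcomes. The intervention-arm proportion is then less precise than its binomial variance suggests.

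Two things would follow. Simple intervals for the RR and NNT would be too narrow, and the trial would have less power than stated. The second matters more at the protocol stage. An analysis plan can still choose a suitable interval, but it cannot restore patients who were never recruited, nor use a group identifier that was never recorded.

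**Working it through.** **Inputs from the article.** Rates 15% and 35%; power 80%; alpha 0.05; 73 per arm, recruited 95 per arm; 30% attrition; 7 units.

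**Assumptions, because the article gives neither figure.** ICC from 0.01 to 0.10, counting only correlation caused by delivery; intervention patients spread evenly over all 7 units.

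**Step 1: reproduce the stated sample size.** Two-sided, pooled variance, no continuity correction:

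n = [1.96·√(2·0.25·0.75) + 0.842·√(0.15·0.85 + 0.35·0.65)]² / 0.20² = (1.200 + 0.501)² / 0.04 = 72.4, so 73 per arm.

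This matches the article with no design effect. The stated power therefore assumes independent patients.

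**Step 2: variance with clustering in one arm.** The design effect is DE = 1 + (m − 1)·ICC, applied to the intervention arm only.

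- Risk difference: true SE / simple SE = √[(0.1275 + 0.2275·DE) / 0.355]
- Log RR: true SE / simple SE = √[(5.667 + 1.857·DE) / 7.524], where 5.667 = 0.85/0.15 and 1.857 = 0.65/0.35

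With all 95 analysed, m = 95/7 = 13.6. After 30% loss, m = 66.5/7 = 9.5.

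- Lower end (m = 9.5, ICC 0.02): DE = 1.17; risk difference ratio 1.05; log RR ratio 1.02.
- Upper end (m = 13.6, ICC 0.05): DE = 1.63; risk difference ratio 1.18; log RR ratio 1.075.

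**Step 3: power at 73 per arm.** Here m = 73/7 = 10.4 and power = Φ(0.20/SE − 1.96), with SE = √[(0.1275 + 0.2275·DE)/73]. This formula is unpooled, so it gives 81.8% at ICC 0, against 80.3% by the pooled formula of Step 1. Compare only within the column.

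| ICC | DE | SE ratio, risk difference | SE ratio, log RR | Power |
|---|---|---|---|---|
| 0 | 1.00 | 1.00 | 1.00 | 81.8% |
| 0.01 | 1.09 | 1.03 | 1.01 | 79.5% |
| 0.02 | 1.19 | 1.06 | 1.02 | 77.3% |
| 0.05 | 1.47 | 1.14 | 1.06 | 71.0% |
| 0.10 | 1.94 | 1.27 | 1.11 | 62.0% |

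At the planning rates and ICC 0.05, the RR of 2.33 has a 95% interval of 1.20 to 4.54 rather than 1.24 to 4.38. The NNT of 5 has an interval of about 2.8 to 22.7 rather than 3.0 to 15.8. With m held at 10.4, 80% power needs about 91 evaluable per arm. Adding patients to the same seven units raises m: with 95 evaluable per arm (m = 13.6), power is 78.9%.

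**Step 4: smaller clusters.** If sessions run in assumed groups of 5 and correlation arises within groups only, ICC 0.05 gives DE = 1.20. The true SE is then about 6% larger for the risk difference and 2.4% larger for the log RR.

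**The case against.** A reader might infer that the plan's intervals do treat intervention patients as independent and are therefore too narrow. The article does not support this. It names no interval method and excludes neither robust standard errors nor a mixed model. A condensed article commonly leaves such detail to the analysis plan. The absence of a unit or therapist identifier from the listed variables is likewise no proof that none is recorded.

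A reader might also infer a false-positive rate above 5%. With equal rates in both arms, the error of a simple test is 2·[1 − Φ(1.96/√((1 + DE)/2))], or 6.0% to 8.7% for DE 1.17 to 1.63. But this needs delivery effects that differ between units or groups while averaging zero. If the programme does nothing for anyone, sharing a physiotherapist creates no correlation and the error stays at 5%.

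Three further objections have weight. Both arms come from the same centres, so a centre effect common to both largely cancels; only delivery-induced correlation counts, and the training aims to reduce it. On the RR scale the control arm supplies most of the variance, so the effect there is modest. Group delivery is inferred from general remarks on socialisation and is not stated in the Intervention section.

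On the other side, training does not remove the effect of sharing a group. Seven is the largest number of units available, so using fewer would make unit-level clusters larger. The sample size is fixed in this document, and it demonstrably contains no allowance.

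**Conclusion.** The point holds in conditional form. It is established that delivery is shared in one arm only, that the 80% power assumes independence, and that the article describes no handling of intervention-arm clustering. It is not established that the intervals will be wrong: that requires both simple formulas and a delivery-induced ICC above zero.

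Under the assumed ICC of 0.02 to 0.05 and unit-level clusters, the understatement is moderate for the risk difference and NNT and small for the RR. The loss of power is the larger practical consequence: negligible at ICC 0.01 and about 11 percentage points at ICC 0.05 (81.8% to 71.0%). At ICC 0 nothing changes. No general claim of type I inflation is warranted. This is an inexpensive improvement to the plan and does not show that the main analysis is invalid.

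**What to change.** 1. Record physiotherapy unit, physiotherapist and exercise group for every intervention patient in the electronic data collection notebook.
2. Report the RR and the risk difference with NNT using intervals that allow for intervention-arm clustering: standard errors clustered on the delivery unit, with controls as singletons and a small-sample correction because clusters are few, or a partially nested model. Do this at least as a pre-specified sensitivity analysis.
3. State under Sample size that the 80% power assumes no clustering, ideally with power at one or two assumed ICC values.

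The cost is a few data fields and some wording, slightly wider intervals and a slightly lower stated power. One practical point concerns blinding. The plan keeps outcome assessors and the statistician blind to allocation, and a cluster code that exists in one arm only reveals it. The identifiers should be hidden from assessors, and the cluster-aware code should be fixed before they are released to the statistician.
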